### 2.6. Interventions

Patients providing written informed consent will be randomized to TiTo-SHB or C.

#### 2.6.1. TiTo-SHB Group

The structured home-based TiTo walking program will be prescribed during serial visits to the hospital [21,22,23]. The program will include two 8-min sessions per day (6 days/week) of intermittent walking (1 min of exercise and 1 min of seated rest) at a prescribed speed converted into a walking cadence and followed at home using a digital metronome or a smartphone application. The walking sessions will preferably be performed overground indoors at home (e.g., in a hallway or a heated garage) to avoid the influence of weather or on a treadmill if preferred by the patient. During the trial, 3 follow-up visits (at weeks 5, 12 and 19) will be performed to evaluate patient adherence to the program and to update the exercise program, with the duration of each session remaining constant. The intensity of each walking bout will be progressively increased according to a precise scheme (Table 1). The patients will be asked to fill out a daily training record indicating completion of the exercise and any associated symptoms. Patients will be permitted to contact the rehabilitation team, composed of a physician and an exercise physiologist, by telephone throughout the study period. During the first hospital visit, a demonstrative training session will be executed with each patient.

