#### 2.6.2. Control Group

Patients randomized in this group after the baseline outcome measurement session will be advised to walk as suggested by the guidelines [1,5]. In particular, a team member will recommend that patients walk for approximately 30 min at least 3 times per week; when the patient faces claudication pain, he/she will be allowed to rest and resume walking as soon as possible. A daily log will be provided to each patient to record and compile the amount of walking performed.

All patients will undergo optimization of medical therapy by the vascular surgeon. Both interventions will last 6 months.

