Long-term clinical outcomes, in terms of PAD-related revascularization, all-cause hospitalizations and survival probability, will be collected at 6, 12 and 24 months.

All outcome measurement sessions will be carried out in the same indoor temperature-controlled environment between 8.00 a.m. and 1.00 p.m.

The participant timeline of the trial is reported in Table 2.

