### 2.10. Harms

The safe exercise procedures encompassed in this trial, along with the rigorous handling of potential harm as a local hospital policy, are expected to minimize all the potential risks. However, any potential adverse events will be recorded and treated according to the Ferrara University Hospital regulations.

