### 2.12. Statistical Analysis

Standard analysis methods for randomized controlled trials will be employed. The distribution of the data will be assessed with the Shapiro-Wilk test. Between-group comparisons at baseline will be performed with Student’s t-test, the Mann-Whitney test, or the chi-squared test according to the nature and distribution of the data. Between-group differences in all outcomes according to the trial hypotheses will be tested with Student’s t-test or the Mann-Whitney U test as appropriate. Within-group outcomes will be assessed using the paired-samples t-test or the Wilcoxon signed-rank test. In case of baseline differences between groups, appropriate adjustment measures (e.g., analysis of covariance) will be carried out. An intention-to-treat analysis will be used, with missing values replaced using the multiple imputation procedure (although all efforts will be made to minimize their incidence). A sensitivity analysis (e.g., per protocol) will also be performed to test the stability of the conclusions.

Moreover, Kaplan–Meier analysis and Cox regression will be used to model the incidence rates of long-term clinical outcomes (hospitalization and death). Subgroup analyses will be scheduled to determine the impact of the findings in smaller populations (e.g., to determine gender differences [40], etc.). Kaplan-Meier estimates of the distribution of times from the beginning of rehabilitation to the clinical events and a log-rank test for trend will be used to compare the curves of the patient groups. A p value < 0.05 will be considered significant. Data will be analyzed using SPSS 21.0 (IBM, Armonk, NY, USA) and MedCalc statistical software (version 19.8 and later, MedCalc Software bvba, Ostend, Belgium).

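### Symptoms are asked for daily, with three interim visits and telephone access, only in the TiTo-SHB arm, so minor adverse events may be ascertained unequally

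*Protocol article*

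**What the plan says.** **TiTo-SHB arm (section 2.6.1).** Patients complete a "daily training record indicating completion of the exercise and any associated symptoms". In addition, "3 follow-up visits (at weeks 5, 12 and 19) will be performed to evaluate patient adherence to the program", and the programme is updated at those visits. The same section adds: "Patients will be permitted to contact the rehabilitation team", by telephone, throughout the study.

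**Control arm (section 2.6.2).** "A daily log will be provided to each patient to record and compile the amount of walking performed". No symptom field is described, nor any visit or telephone line between baseline and the 6-month assessment. Table 2 likewise lists no assessment common to both arms between those two points.

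**Harms (section 2.10).** "any potential adverse events will be recorded and treated according to the Ferrara University Hospital regulations". This is not limited to one arm. How patients are asked about events, and when, is not stated.

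**Clinical events (section 2.7).** PAD-related revascularization is collected together with "all-cause hospitalizations and survival probability, will be collected at 6, 12 and 24 months". This too is not limited to one arm.

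**Analysis (section 2.12).** Kaplan-Meier and Cox methods are planned for hospitalization and death. No between-arm analysis of symptoms or adverse events is named.

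**The concern.** Both arms keep a daily diary and the article describes the content of each, so the difference between them is stated and is more than an omitted detail. One diary prompts for symptoms; the other, as described, does not. The arm with the prompt also has three extra occasions to report to staff and a stated route to telephone them. Patients who are asked more often tend to report more. A table of recorded events by arm could then reflect how events were sought as well as how often they occurred.

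Three features of this trial make that matter.

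- The rationale is a pain-free programme set against advice under which patients may walk into claudication pain, rest and resume. Symptoms during exercise are a natural place to look for a difference between the arms.
- The Conclusions foresee extending the programme to frail patients and to those with more severe disease, a step for which readers will want to know how well it was tolerated.
- Participants are not blinded (section 2.5). Blinding of the outcome assessors does not protect what patients report about themselves between assessments, so equal questioning is one of the few protections left.

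The gap also has to be closed during data collection. Symptoms never asked for in controls cannot be recovered at the analysis stage.

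**Working it through.** The plan states no adverse event figure to reproduce, so the check sets the two arms' data capture side by side for the six months of intervention.

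| Route by which a minor event could be learned | TiTo-SHB (2.6.1) | Control (2.6.2) |
|---|---|---|
| Daily diary | Exercise completion and symptoms | Walking amount |
| Interim hospital visits | 3 (weeks 5, 12, 19) | None described |
| Telephone access to the team | Stated | Not stated |
| General recording of adverse events (2.10) | Applies | Applies |
| Enquiry at 6 months (2.7, Table 2) | Applies | Applies |

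**Opportunities to report.** Table 1 runs for 24 weeks and section 2.6.1 prescribes 6 training days per week, so the symptom record covers up to 24 x 6 = 144 training days in TiTo-SHB. Adding the visits gives 144 + 3 = 147 occasions, before any telephone calls. The corresponding number described for controls is 0.

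**From opportunity to bias.** Let c_T and c_C be the probabilities that an event, once it has occurred, is recorded in the TiTo-SHB and control arms. Then

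observed risk ratio = true risk ratio x (c_T / c_C).

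The rows that differ all favour c_T > c_C, so the likely direction is towards more recorded events in TiTo-SHB. The article gives neither c_T nor c_C, and no event rate, so the factor c_T / c_C cannot be calculated. The count of 147 against 0 measures opportunity, not bias.

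**Which events are exposed.** The argument needs an event whose recording depends on the patient being asked, such as muscle or joint pain, claudication during a session, or a fall without a hospital stay. It does not carry over to revascularization, hospitalization or death, which section 2.7 collects in both arms at the same time points and which do not depend on a diary.

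**Whether section 2.10 closes the gap.** It sets the intention to record events in everyone. It gives no common method of asking, so the routes described for the six months remain those in the table.

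**The case against.** The strongest case against the point has five parts.

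1. *The comparison is not planned.* Section 2.12 names no between-arm test of symptoms or adverse events, and safety is not among the stated aims. This stands, and it limits the point to any by-arm summary that is produced. A descriptive table of events by arm would carry the same bias without any test.

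2. *The training record is not a harms instrument.* It sits under Interventions, and the stated purpose of the visits is to evaluate adherence and update the programme. This is fair: nothing in sections 2.7, 2.9, 2.10 or 2.12 makes the record a source for harms. Nothing rules it out either, and a symptom written there or mentioned at a visit falls within the broad wording of section 2.10. A statement either way would settle it.

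3. *The forms and hospital regulations are not shown.* An article condenses, and the control log may contain a symptom field. This lowers confidence. It does not remove the difference in the two descriptions that are given.

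4. *A symptom field changes the comparator.* Section 1 lists self-monitoring tools among the components of structured home-based programmes, so symptom monitoring moves the controls slightly towards the intervention. This is a genuine cost and is the reason for the alternative under the fix.

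5. *Symptoms are measured equally elsewhere.* Pain-free walking distance and VascuQoL-6 are collected in both arms, and outcome assessors are blinded. This stands. A reader might infer that the symptomatic contrast between pain-free and walk-to-pain exercise cannot be shown at all, and that would be wrong.

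Two further inferences are tempting and unsupported. One is that every harms comparison in the trial is biased; the shared collection of revascularization, hospitalization and survival contradicts it. The other is that control-arm events are in fact missed; section 2.10 applies to all patients, so under-recording is a risk that the article does not establish.

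**Conclusion.** The point holds for minor, patient-reported and exercise-related adverse events. The plan as described asks about symptoms daily in one arm only, adds three visits and telephone access in that arm, and states no common method of enquiry. Such events may be ascertained unequally, most likely with more recorded in TiTo-SHB, and a by-arm summary of them could not be read as a comparison of tolerability.

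The size is unknown. A reader might be tempted to assume capture rates and quote an apparent relative risk, but any such figure would only return the assumptions put into it. The direction is more secure than the magnitude.

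The conclusion rests on two assumptions: that the control log contains what section 2.6.2 describes and no more, and that the hospital regulations cited in section 2.10 do not already impose the same scheduled enquiry in both arms. If either is wrong, the concern shrinks or disappears. The primary outcome and the long-term clinical outcomes are untouched by this argument.

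**What to change.** **Preferred change.**

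- In section 2.6.2, add to the existing control log the same symptom and adverse event field that TiTo-SHB patients complete.
- In section 2.10, state that any between-arm summary of harms uses only sources common to both arms: the matched log, and the same enquiry at the shared 6- and 12-month time points.
- In the same place, state that events learned only at TiTo-SHB visits or through telephone calls are listed separately and do not enter the comparison.

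**Alternative.** If the sponsor prefers not to add symptom monitoring to the comparator, state that TiTo-SHB diary symptoms serve training monitoring only and are not compared between arms.

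**Cost.** The preferred change needs one field on a form that controls already fill in and a short addition to section 2.10. Its downside is slightly more burden and self-monitoring in the control arm. It also does not make capture perfectly equal, since the interim visits may keep TiTo-SHB diaries better completed. The alternative leaves the comparator unchanged and needs one sentence, but gives up any comparison of day-to-day exercise symptoms.

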#### 2.6.2. Control Group

Patients randomized in this group after the baseline outcome measurement session will be advised to walk as suggested by the guidelines [1,5]. In particular, a team member will recommend that patients walk for approximately 30 min at least 3 times per week; when the patient faces claudication pain, he/she will be allowed to rest and resume walking as soon as possible. A daily log will be provided to each patient to record and compile the amount of walking performed.

All patients will undergo optimization of medical therapy by the vascular surgeon. Both interventions will last 6 months.

### 2.7. Outcomes

The outcome measures will be performed at study entry prior to randomization (T0), at the end of the training program (6 months, T1) and after the 12-month follow-up (T2).

The primary outcome measure will be the 6-min walking test [35]. Patients will be asked to walk back and forth in a standard 20-m corridor with the goal of covering as much distance as possible in 6 min. Patients will be asked to report the distance at which claudication symptoms began, which will be recorded as pain-free walking distance (PFWD). When necessary, they will be allowed to stop as needed and restart whenever possible. The total distance walked, or 6-min walking distance (6MWD), will be measured. Heart rate will be continuously measured throughout the test with a heart rate monitor, and maximal oxygen consumption may be calculated according to the published formulas. The rate of perceived exertion (RPE), according to the 1-10 Borg RPE scale, will be collected at the end of the test [36]. The minimal clinically important difference for 6MWD will be set at 36 m [37].

Secondary outcomes will include the following:

The ABI will be measured according to published standards [38]. With the patients lying in a supine position, blood pressure values at the posterior tibial and dorsalis pedis arteries will be collected, along with systolic blood pressure. The ratio of the highest value measured in each leg to the pressure measured in the arm will be used to obtain the ABI values.

The Vascular Quality of Life Questionnaire-6 (VascuQoL-6) is composed of 6 questions that assess the impact of PAD on patients’ quality of life in the previous two weeks. The scores range from 6 to 24, where a higher score corresponds to a better QoL [39].

Foot temperature will be measured with an infrared thermal camera (FlirOne Pro, Flir, Milan, Italy) at three points on the dorsum of each foot: the posterior tibial artery behind the malleolus, the anterior tibial artery at the ankle, and the dorsalis pedis artery on the dorsum of the foot.

A five-time sit-to-stand test will be used to measure lower limb strength. The patient will sit with both arms folded across his/her chest, and he/she will be asked to stand and sit five times consecutively, aiming to complete them as quickly as possible. The total elapsed time will be recorded.

Long-term clinical outcomes, in terms of PAD-related revascularization, all-cause hospitalizations and survival probability, will be collected at 6, 12 and 24 months.

All outcome measurement sessions will be carried out in the same indoor temperature-controlled environment between 8.00 a.m. and 1.00 p.m.

The participant timeline of the trial is reported in Table 2.

### 2.8. Sample Size Calculation

Based on published data we observed the variations in 6MWD in TiTo-SHB program and in other trials including groups at usual care [20,23]. Considering a baseline mean 6MWD of 300 m, with 27 patients for each group, the study will have 90% power to confirm the superiority of TiTo-SHB respect to walking advice, with a superiority margin set at the minimal clinically important difference or 36 m [37]. Allowing for a possible 10% dropout rate during the trial, a sample size of 60 patients (30 per group) will be planned.

### 2.9. Data Protection and Management

A researcher blinded to the treatments will collect outcome measures and will create a password-protected electronic database containing all the data collected. Another researcher will check the completeness of the data, and he/she will randomly select some clinical records to verify that the outcomes were correctly inserted in the database.

Patients’ personal data will be treated according to the current regulations, including the 2016/679 European Union act and the D.Lgs. 30 giugno 2003, n. 196 s.m.i. Italian regulation as well as any possible adjunctive measures deemed applicable by the Italian Data Protection Authority.

### 2.10. Harms

The safe exercise procedures encompassed in this trial, along with the rigorous handling of potential harm as a local hospital policy, are expected to minimize all the potential risks. However, any potential adverse events will be recorded and treated according to the Ferrara University Hospital regulations.

### 2.11. Data Monitoring, Auditing and Interim Analyses

Owing to the single-center design of this study, a Data Monitoring Committee will not be required. Audits will be periodically scheduled with the Ferrara University Hospital clinical research office to verify the compliance of the trial with the ethical standards. The research coordinator will be in charge of the interim analysis and the final decision to stop, modify or terminate the trial.

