### 2.5. Randomization and Blinding

A team member responsible for the enrollment will generate the allocation sequence on a personal password-protected computer, with access granted only to the research coordinator and the administrator. Then, in order to prevent selection bias, patients will be randomized between the two groups through a computerized randomization stratification approach by an external administrator not involved in the trial. Participants will be stratified by their degree of PAD severity (ankle-brachial index [ABI] > or <0.5) and the presence of diabetes. The randomization scheme (1:1 ratio) will be structured in permuted blocks of 8 to ensure a similar number of participants between groups. Ultimately, each of the subjects will be assigned to receive one of two treatments: TiTo-SHB (experimental group) or walking advice as an active control (C). The participants cannot be blinded to the two interventions, as the training protocol is detailed in the information form. Once randomized, a participant will not be transferred to the other treatment group for any reason (even at the participant’s request), but the treatment may be suspended upon the patient’s request or the physician’s decision.

Researchers responsible for outcome measurement will be blinded to group allocation; unblinding will not be possible for any reason.

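### The research coordinator, who has access to the allocation sequence, runs the interim analysis and holds the final decision to stop or modify the trial, with no independent review of interim results

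*Protocol article*

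**What the plan says.** All references are to the protocol article.

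- **Interim analysis and decision (Section 2.11).** "The research coordinator will be in charge of the interim analysis and the final decision to stop, modify or terminate the trial". The power covers modification as well as stopping, and nothing bars the use of outcome data.
- **Independent review (Section 2.11).** "Owing to the single-center design of this study, a Data Monitoring Committee will not be required". The only outside check named there is periodic audit with the hospital's clinical research office, and its stated purpose is "to verify the compliance of the trial with the ethical standards".
- **Allocation (Section 2.5).** The sequence is generated on a password-protected computer, "with access granted only to the research coordinator and the administrator".
- **Blinding (Section 2.5).** "Researchers responsible for outcome measurement will be blinded to group allocation; unblinding will not be possible for any reason". The coordinator is not described as blinded.
- **Significance level (Section 2.12).** "A p value < 0.05 will be considered significant". No sidedness is given and no interim look is mentioned.
- **Sample size (Section 2.8).** "with 27 patients for each group, the study will have 90% power to confirm the superiority of TiTo-SHB respect to walking advice". The margin used is 36 m, taken as the smallest change that matters to patients. No interim look is mentioned here either.

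**The concern.** Three things that are normally kept apart meet in one role: the means of knowing who is in which arm, charge of the interim analysis, and authority over whether and how the trial continues. A person running the trial who knows interim results by arm can act on them, consciously or not, in recruitment, in follow-up effort or in the emphasis given to outcomes. The last risk is concrete here. Section 2.7 makes the 6-minute walking test primary, whereas Table 2 labels pain-free walking distance as primary and 6-minute walking distance as secondary. Modifying the trial with by-arm results in view would leave that choice open to challenge.

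The reason given for having no committee does not meet this point. The number of sites has no bearing on whether interim results should be withheld from the trial team, and a single site tends to concentrate roles. A trial of 60 patients can reasonably do without a committee. The difficulty lies in combining that choice with an interim analysis run from inside the trial.

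There is a second, conditional stake. If the look can lead to a claim of efficacy at the same 0.05 used at the end, the overall false-positive rate rises above 5%, and a trial stopped on a favourable early result tends to overstate the effect.

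**Working it through.** **1. The plan's own figure.** Section 2.8 gives 27 per group and 10% dropout: 27 / 0.9 = 30 per group, 60 in total. This step reproduces. The 27 itself cannot be reproduced, because neither a standard deviation (SD) nor an expected difference is stated.

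**2. Who holds what.**

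| Function | Holder | Section |
|---|---|---|
| Access to allocation sequence | coordinator and administrator | 2.5 |
| Promised blinding | outcome assessors | 2.5 |
| Interim analysis | coordinator in charge | 2.11 |
| Decision to stop, modify or terminate | coordinator in charge | 2.11 |
| Independent review of interim results | none named; committee declined | 2.11 |

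This part of the point needs no arithmetic.

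**3. Type I error if the look is an efficacy test.** Assumptions that are not in the document: a two-sided test, |Z| > 1.96 at every analysis, and a trial that can claim benefit at the interim. For one look at information fraction t, Z1 and Z2 are bivariate normal with correlation √t, and

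overall error = 1 − P(|Z1| < 1.96 and |Z2| < 1.96).

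| Information at the look | Correlation √t | Overall error |
|---|---|---|
| 25% | 0.500 | 9.1% |
| 50% | 0.707 | 8.3% |
| 75% | 0.866 | 7.3% |

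Two equally spaced looks plus the final analysis, simulated with 2,000,000 replicates, give 10.7%. A look for safety or futility only adds no chance of a false claim of benefit, so there is no inflation.

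**4. The same formula with a strict interim boundary.** With p<0.001 at half information and 0.05 at the end (Haybittle-Peto), the overall error is 5.02%. A final threshold of 0.05 is therefore compatible with a sound interim plan.

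**5. What a half-way look could show.** Suppose 36 m is the assumed difference, which is one possible reading of Section 2.8. The SD implied by 27 per group, 90% power and two-sided 0.05 is then 36 / [√(2/27) × (1.960 + 1.282)] = 36 / 0.882 = 40.8 m. With 15 per arm, half of the 30 planned, the 95% confidence interval half-width is about 1.96 × 40.8 × √(2/15) = 29 m. That is most of the 36 m minimal important difference, and a larger SD would widen it.

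**The case against.** The strongest reply is that Section 2.11 never says the interim analysis compares walking outcomes by arm or can stop the trial for benefit. It stands in a section on monitoring and audit, directly after Harms, and fits a look at safety, recruitment, data quality or futility equally well. Timing, endpoint and boundary are often left to a full protocol or analysis plan, and neither is shown. This stands. The absence of those details is no fault of the article, and the error figures above are illustrations under stated assumptions.

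Three stronger readings are tempting and are not supported:

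- **That the trial's false-positive rate exceeds 5%, or that the significance rule is invalid.** This needs an efficacy look at an unadjusted threshold, which the document does not state. Keeping 0.05 at the end is no error in itself, as step 4 shows.
- **That the coordinator decides alone.** The text says only that the coordinator is in charge. No other decision-maker is named and a committee is declined, but sole authority remains an inference.
- **That the coordinator will see results by arm.** Section 2.9 has a blinded researcher collect outcomes and build a separate protected database, and nothing says it is linked to the allocation sequence for the interim look. What the text supports is that the coordinator is able to know.

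The audits do not fill the gap, since their stated scope is ethical compliance. The sentence in Section 2.5 that rules out unblinding is attached to the outcome assessors and does not clearly reach the coordinator.

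What the reply leaves untouched is the arrangement that the article does fix. A boundary written in another document would not separate the roles.

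**Conclusion.** The point holds as one about independence. Sections 2.5 and 2.11 place access to the allocation sequence, charge of the interim analysis and the final decision to stop or modify with one trial insider, and the single-centre reason does not justify the lack of independent review. The resulting bias cannot be given a size from the document.

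The type I error part is conditional only: about 7.3% to 9.1% for one unadjusted two-sided efficacy look, 10.7% for two equally spaced looks, and no inflation if the look is for safety or futility only. The amendment is a cheap improvement that should be made. The point does not show that the planned final test is wrong.

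**What to change.** Amend Section 2.11 to state that:

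- the interim look covers only safety, recruitment and data completeness;
- no walking outcomes are compared by arm;
- the trial is neither stopped for efficacy nor modified on outcome data.

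The final 0.05 in Section 2.12 then stands unchanged.

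If stopping for efficacy is wanted, allow one look at half information with p<0.001 (Haybittle-Peto; overall error about 5.02%, final test still at 0.05). It should be computed by a person who is not the coordinator and has no role in running the trial.

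The first option costs a few sentences and needs no committee and no extra patients. What is lost is the freedom to stop early for benefit, which has little value with 60 patients and about 15 per arm at half-way.
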